#### *Sample size*

We will randomly select eight long-term care homes that agree to join this study. As no similar cluster-randomized trial has been reported in the literature, we can only estimate the intracluster coefficient with a range between 0 and 0.1 [22]. The intensity of pain can vary according to the different natures and sources of the pain. As this study is not limited to participants suffering from a particular type of pain, we anticipate that variations in the nature of participants’ pain will be considerable. Due to its heterogeneous nature, we assumed an intracluster correlation of 0.02. The pilot study was able to detect a mean difference of 13.41 points on the MSQ score (95% confidence interval 8.923 to 17.897) and -0.3 points on the C-PAINAD (95% confidence interval -4.459 to 0.169) between the pre- and post-tests [18]. After averaging the effect sizes calculated based on these two mean differences, this was equivalent to an effect size of 0.65. In order to secure an appropriate effect size, a more conservative approach of using an effect size of 0.4 was used to calculate the sample size. With a significance level (α) of 0.05 and power (1-β) 0.8 for a two-sided test, the sample size calculation gives about 38 participants for each group in order to evaluate a mean difference in MSQ and C-PAINAD scores between the experimental and control groups. Accounting for the intracluster correlation, a variance inflation factor of 1.31 will be multiplied to this calculated sample size. Further accounting for a 15% drop-out rate over the period based on two similar studies [13,18], a total number of 61 participants per group is required, resulting in a total proposed sample size of 122. This means we will recruit 15 to 16 participants in each long-term care home.

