### Randomization and allocation concealment

The care home list is generated from the website of the Social and Welfare Department of HK, which includes all local government-funded long-term care homes. An invitation letter has been sent to 75 local long-term care homes that meet the home selection criteria. Based on our previous experience, the response rate will be around 15% to 20%. This means we anticipate that about 11 to 15 care homes will accept our invitation. A random list and a replacement list will be generated. Eight care homes will be randomly selected from all care homes who accept the invitation.

The homes will then be randomized to the control or experimental condition according to the pre-set computer-generated randomization list generalized by a biostatistician who will not be involved in this study. Random group allocations will be sealed in opaque envelopes. Each care home will be viewed as one unit throughout the entire study. As mentioned in the section on home selection criteria, the settings of the home should be similar, and we will not stratify or match the homes during the randomization process. Random allocation will be performed after receiving the homes’ indication of their willingness to join the study. We anticipate that this recruitment process will take about 3 to 4 months. The researcher will then open the random allocation envelopes in order and allocate nursing homes to either the experimental or control condition accordingly. Participants from each long-term care home will be placed into their care homes’ corresponding group to avoid ‘contamination’ effects across participants within the experimental and control conditions. Participant recruitment will be conducted after the care homes have been randomly allocated to either group. Each care home will recruit 15 to 16 participants. We anticipate that it will take about 3 to 4 weeks to complete participant recruitment in each nursing home. The study, including staff training, baseline assessment, and protocol implementation, will start after we have recruited sufficient numbers of participants in each nursing home.

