### Outcome measures

The effectiveness of the Protocol on pain management will be evaluated by: (1) the use of pharmacological pain treatments, measured by the Medication Quantification Scale III (MQS III); (2) the use of all non-pharmacological pain treatments recorded on the participants’ pain management record; and (3) pain-related behaviors exhibited by participants, which will be assessed by an observational pain scale (that is, C-PAINAD). The Protocol will be used to guide the pain management of the participants in the experimental condition for 12 weeks (that is, from the fifth to the sixteenth weeks of the intervention cycle). Intervention effects will be measured weekly and compared with the baseline measurements as well as between the experimental and control conditions to detect the progress of the effectiveness of the Protocol in pain management continually throughout the study period. Baseline measurements will be collected for 4 weeks (that is, between the first and fourth weeks of the intervention cycle).

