### Statistical analysis and outcome measurement

Data will be analyzed using the Statistical Package for the Social Sciences (SPSS 19). Descriptive statistics will be generated for the demographic data. Normality assumptions for the variables will be checked. The paired t-test or Wilcoxon’s signed rank test will be used to examine any significant difference in the use of pain treatments and the change in the C-PAINAD score in the experimental group before and after implementation of the protocol. Student’s t-test or the Mann-Whitney U test will be used to examine any significant differences between the control and experimental groups in terms of the outcome variables. For categorical and dichotomous outcome variables, a χ2 test will be used to identify any significant differences between the groups. A *P* value ≤0.05 will be considered statistically significant. Mixed effect modelling (MEM) will be further used to take into account the intracluster correlation, to measure changes in the outcome measures after intervention with respect to its baseline, and to see the effectiveness of the intervention.

Multiple imputations will be adopted to manage all the missing data.

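### Unadjusted resident-level tests are stated as significance tests between arms in a trial that randomises homes, and are not made subordinate to the planned mixed model

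*Protocol article*

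**What the plan says.** **Design.** Under Randomization and allocation concealment: "The homes will then be randomized to the control or experimental condition". The same section adds: "Each care home will be viewed as one unit throughout the entire study". The Sample size section fixes the number of homes: "We will randomly select eight long-term care homes that agree to join this study". It assumes an ICC of 0.02, gives 0 to 0.1 as the possible range, and multiplies the sample by 1.31 for clustering.

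**Analysis.** The section Statistical analysis and outcome measurement names, in this order:

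- a paired t-test or Wilcoxon's "signed rank test will be used to examine any significant difference in the use of pain treatments" and in the change of C-PAINAD score, before versus after, in the experimental group only;
- Student's "t-test or the Mann-Whitney U test will be used to examine any significant differences between the control and experimental groups" on the outcome variables;
- for categorical and dichotomous outcomes, "a χ2 test will be used to identify any significant differences between the groups";
- a significance threshold of P ≤0.05;
- then: "Mixed effect modelling (MEM) will be further used to take into account the intracluster correlation". The rest of that sentence gives the model the further tasks of measuring change from baseline and assessing whether the intervention works.

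No adjustment for home is stated for the first three items, and no order of precedence is given between them and the mixed model.

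**The concern.** A t, Mann-Whitney or chi-square test on residents takes every resident as an independent observation. Residents of one home share staff, physicians and routines, and the whole home goes to one arm. If outcomes are correlated within homes, the variance of the arm difference is larger than these tests assume and their P values are too small. The article accepts that correlation when it sets the sample size and then leaves it out of the tests it names first.

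A chance difference between one set of homes and another could therefore be reported as a significant effect of the Protocol. If an unadjusted test and the mixed model disagreed, the text as written would support reporting either.

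The within-arm test raises a second, smaller problem. A before–after change in the experimental homes mixes the Protocol's effect with time trend and regression to the mean. Control homes also receive four workshops in the first four weeks, so change over time can occur without the Protocol. Only the comparison with the control arm can isolate its effect.

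**Working it through.** **Inputs**

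- Eight homes, 122 residents, 61 per group, 15 to 16 per home (Sample size). Mean home size m = 122/8 = 15.25.
- Homes per arm: not stated. 61/15.25 = 4, so four per arm is assumed.
- ICC: 0.02 assumed, range 0 to 0.1. Inflation factor 1.31. Drop-out 15%.
- Nominal two-sided level 0.05.
- Assumed: each test uses one value per resident.

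**Step 1. The plan's own inflation factor.** Design effect DE = 1 + (m − 1) × ICC. With m = 15.25: 1 + 14.25 × 0.02 = 1.285. With m = 16: 1 + 15 × 0.02 = 1.30. The stated 1.31 needs m = 1 + 0.31/0.02 = 16.5, slightly above the stated home size. The difference is immaterial here, and both values are carried forward.

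**Step 2. Type I error of an unadjusted test.** Its standard error is too small by a factor √DE, so the actual error is 2 × [1 − Φ(1.96/√DE)].

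| ICC | DE | 1.96/√DE | Actual error |
|---|---|---|---|
| 0 | 1.000 | 1.960 | 5.0% |
| 0.02 | 1.285 | 1.729 | 8.4% |
| 0.02, plan's factor | 1.310 | 1.712 | 8.7% |
| 0.05 | 1.7125 | 1.498 | 13.4% |
| 0.10 | 2.425 | 1.259 | 20.8% |

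**Step 3. Simulation for each named test.** Null trials with homes of 15, 15, 15 and 16 residents in each arm and a normally distributed outcome; 40,000 trials per ICC (15,000 for Mann-Whitney). The chi-square test is applied to the score dichotomised at its mean. The last column is a t-test on home means, with 8 − 2 = 6 degrees of freedom.

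| ICC | t | Mann-Whitney | Chi-square | Home means |
|---|---|---|---|---|
| 0 | 5.0% | 5.0% | 5.8% | 5.0% |
| 0.02 | 8.3% | 8.0% | 7.8% | 4.9% |
| 0.05 | 13.6% | 12.8% | 11.4% | 5.0% |
| 0.10 | 20.8% | 20.0% | 16.8% | 4.9% |

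The chi-square figures are lower at higher ICC because dichotomising reduces the correlation within homes. The 5.8% at ICC 0 reflects the discreteness of counts, not clustering.

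**Step 4. After drop-out.** 15.25 × 0.85 ≈ 13 per home. At ICC 0.02, DE = 1 + 12 × 0.02 = 1.24 and the error is 7.8%. At ICC 0.10, DE = 1 + 12 × 0.10 = 2.20 and the error is 18.6%. Simulation at 0.02 and 0.10 gives 7.9% and 19.1% (t), 7.3% and 18.5% (Mann-Whitney), and 8.4% and 16.2% (chi-square).

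These error rates depend on home size and ICC only; the pre-inflation sample size and the effect size do not enter.

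**The case against.** The strongest reply is that clustering is dealt with. The mixed model is planned explicitly for the intracluster correlation, and it is the only method in the section expressly tied to the effectiveness of the intervention. On that reading the simple tests are preliminary. This stands as far as it goes: the documents do not support a reader's inference that the analysis as a whole ignores clustering, or that the trial's conclusion carries the error rates above. But the simple tests are worded as tests of significant differences between groups on the outcome variables, they fall under the stated threshold, and the model is only added to them. That is something the article states, not something it leaves to an analysis plan.

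A second reply is that the inflation is modest at the planning value and that the upper figures need the extreme of the ICC range. This also stands. The range starts at 0, where there is no inflation from clustering, and one range should not be quoted for all three tests.

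A third is that random-effects structure, degrees of freedom and the exact contrast commonly sit in an analysis plan, which is not shown. Agreed; they appear under the fix and are not counted as errors.

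A reader might also infer weekly testing at 0.05 with success claimed on any week, since the Outcome measures section says "Intervention effects will be measured weekly and compared with the baseline measurements as well as between the experimental and control conditions". The article states no such rule, and the mixed model may be what uses the weekly data, so no multiplicity figure is claimed.

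Nor does the article rest its conclusion on the paired test alone: the same sentence sets comparison with baseline beside comparison between conditions.

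**Conclusion.** The point holds in a limited form. The t, Mann-Whitney and chi-square tests, as stated, are not valid tests of the arm difference in this design unless the ICC is 0, and the text does not subordinate them to the mixed model. Their actual type I error at nominal 5% is about 8–9% at the protocol's own ICC of 0.02. At ICC 0.10 it is about 17% (chi-square) to 21% (t-test). With 15% drop-out it is about 7–8% and 16–19% respectively. An analysis on home means holds about 5% throughout.

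These figures assume four homes per arm, about 15 residents per home and one value per resident; the chi-square figures also assume a score split at its mean. They describe the unadjusted tests, not the mixed model.

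The within-arm paired test is a secondary weakness. It cannot be attributed to the Protocol, and no size is claimed for it.

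**What to change.** - State that the mixed model already planned carries the between-arm conclusion. Give it random effects for home and resident, baseline adjustment, and small-sample degrees of freedom, because there are only eight homes.
- For categorical outcomes, replace the chi-square test with a mixed logistic model or a test on home-level proportions.
- Delete the t, Mann-Whitney and chi-square tests as tests between arms, or label them descriptive.
- Label the paired before–after tests in the experimental arm descriptive.

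**Cost.** The change is to wording: no new data and no change in conduct, and the article reports that homes are still being recruited. The price is that P values become less favourable, because they will reflect eight homes and not 122 independent residents.

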## Methods/design

### Study design

A two-group, single-blinded, cluster-randomized controlled trial (RCT) will be used to examine the effect of the Protocol on pain management for older people with dementia as compared to a control condition of usual pain management practice in long-term care homes. This study will take 16 weeks (that is, baseline assessment and care home staff training for 4 weeks and Protocol implementation for 12 weeks). Participants in the control condition will continue usual pain management practice according to their care homes. Intervention effects will be measured weekly and compared with the weekly baseline measurements for 4 weeks, as well as between the experimental and control conditions, to detect the progress of the effectiveness of the Protocol in pain management continually throughout the study period. The overall study design is illustrated in Figure 1.

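### Three unranked outcomes are each tested at an unadjusted 0.05 with no deciding outcome, time point or analysis, so the plan does not hold its 5% error rate

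*Protocol article*

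**What the plan says.** - **Outcome measures** lists three measures on an equal footing: "The effectiveness of the Protocol on pain management will be evaluated by: (1) the use of pharmacological pain treatments" by MQS III, then (2) non-pharmacological treatments and (3) C-PAINAD. None is called primary there or elsewhere.
- **Sample size** does not single one out. It takes the pilot effects on the medication score and on C-PAINAD and combines them: "After averaging the effect sizes calculated based on these two mean differences, this was equivalent to an effect size of 0.65". It then plans "With a significance level (α) of 0.05 and power (1-β) 0.8 for a two-sided test" for both scores together.
- **Study design** and **Outcome measures** describe weekly follow-up. The first says "Intervention effects will be measured weekly and compared with the weekly baseline measurements for 4 weeks". The second says "Intervention effects will be measured weekly and compared with the baseline measurements as well as between the experimental and control conditions". The schedule is "baseline assessment and care home staff training for 4 weeks and Protocol implementation for 12 weeks".
- **Statistical analysis and outcome measurement** prescribes paired tests "in the experimental group before and after implementation of the protocol", two-sample tests between arms on the outcome variables, and chi-square tests for categorical outcomes. The criterion for all of them is that a P "value ≤0.05 will be considered statistically significant". A mixed model is then added to allow for intracluster correlation, to measure change from baseline and to show whether the intervention works. No deciding outcome, time point, order of testing or adjustment is given.

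**The concern.** An error rate of 5% belongs to one pre-specified test. Here several tests share that threshold and none is designated to settle the question. A result on any of the three outcomes, from a between-arm test, a before/after test or the mixed model, meets the stated criterion, and the deciding result can be chosen once the data are seen.

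This matters in this trial because the outcomes may well disagree. Two of them record treatments that the Protocol tells staff to give, so they could rise without any change in pain. In the pilot reported in the Background, the mean medication score rose from 10 to 23.41, while the mean pain score fell only from 2.87 to 2.57 and not significantly. If the main trial repeats that pattern, nothing in the plan says what it means for effectiveness.

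**Working it through.** **Inputs from the article.** Per-test level 0.05, two-sided; 3 outcomes; 12 implementation weeks after 4 baseline weeks; 8 homes; 61 participants per arm; 15% drop-out; assumed intracluster correlation 0.02. The article states no error rate across tests, so the only figure of its own to compare with is 5%.

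**Inputs assumed.** The article gives neither the week-to-week correlation within an outcome nor the correlation between outcomes, so ranges are used.

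**Step 1: one test of one outcome.** The error rate is 0.05, as stated.

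**Step 2: one between-arm test per outcome.** If independent, 1 − 0.95³ = 1 − 0.857 = 0.143, about 14%. With a between-outcome correlation of 0.3, simulated values stay close to this (12 to 14% with no clustering).

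**Step 3: add one before/after test per outcome in the experimental arm.** Six independent tests give 1 − 0.95⁶ = 1 − 0.735 = 0.265. The two kinds of test share the experimental-arm data and so are not independent; the rate was therefore simulated with no Protocol effect. Settings: 4 homes per arm, 13 residents per home (61 × 0.85 ≈ 52 per arm; 52 / 4 = 13), week-to-week correlation 0.5 to 0.95, between-outcome correlation 0.3, no clustering. The last week was compared between arms and with the baseline mean. Result: 22 to 26%.

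At the article's intracluster correlation of 0.02 the same six tests gave 31 to 39%. The extra comes from t-tests that ignore clustering, which is a separate matter and is not counted here. The simulation assumes no time trend; because the before/after test has no control arm, any trend would add to the rate.

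**Step 4, conditional: each implementation week also tested between arms.** That makes 3 × 12 = 36 tests. Simulated share with any |z| > 1.96, between-outcome correlation 0 to 0.3:

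| Correlation between weeks | Any significant result, either direction | Any significant result favouring the Protocol |
|---|---|---|
| 0.9 | 34–35% | 17–19% |
| 0.7 | 51–55% | 27–31% |
| 0.5 | 64–69% | 34–41% |

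Counting only favourable results in step 2 gives 1 − 0.975³ = 0.073, about 7%, against the 2.5% that one two-sided test allows in that direction.

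**Step 5: does a single contrast cure it?** A home-level comparison of mean change from baseline to weeks 5 to 16 stands in here for the mixed model. For one outcome it gave 4.4 to 6.8% in runs of 2,000, scattered around 5%, at intracluster correlations of 0, 0.02 and 0.1. Run on all three outcomes without ranking, it gave 12 to 17%. Making the mixed model decisive is therefore not enough; one outcome must also be chosen.

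**The case against.** The best defence has four parts.

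1. **Weekly testing is inferred.** The statistical section holds the only significance threshold and never prescribes a test per week. The weekly wording elsewhere concerns measuring and following progress, which equally fits a longitudinal mixed model. A reader might infer that the plan runs 36 or more tests and that an ineffective Protocol would very likely come out as significant. The text does not support that. Step 4 is conditional, its correlations are assumed, and its two-sided column counts results against the Protocol that nobody would report as effectiveness. This part of the defence stands.

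2. **The mixed model has a declared purpose.** It is the one analysis said to show whether the intervention works. That is a fair reading and should be acknowledged. But it is worded as an addition to tests that carry the same threshold, and it still covers three unranked outcomes.

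3. **The hypothesis is more structured than any single result.** The Background expects more use of both kinds of treatment, with lower pain scores as a consequence. A rule requiring both would have a much lower error rate. However, this is a hypothesis and is never turned into a decision rule, so it neither licenses a claim from any outcome in any week nor rules one out.

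4. **An analysis plan may settle this.** Details of multiplicity and time points often sit there, and none is shown. Which outcome decides effectiveness is a protocol matter, though, and the article is not silent: it sets an unadjusted threshold over equal outcomes and sizes the trial on an average of two.

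**Conclusion.** The point holds in its limited form. As written, the plan does not keep a 5% error rate and leaves the deciding result open. The rate is about 14% with one between-arm test per outcome, assuming independence. It is roughly 22 to 26% once the before/after tests are included, assuming no time trend and no clustering. The figure of about 34 to 69% applies only if each week is tested separately, with week-to-week correlations between 0.9 and 0.5; it should not be quoted as the plan's error rate.

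A reader might also infer that observer-rated C-PAINAD has to be the primary outcome because the other two reflect what staff are told to do. The article does not settle this: its first objective is treatment use and its second is pain scores. The choice is the sponsor's. The defect should be corrected before outcome data exist, because it determines what the trial can conclude; the article reports that homes were still being recruited.

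**What to change.** In the outcome and analysis sections:

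- Name one primary outcome, chosen by the sponsor and consistent with the two objectives in the Background.
- Name one deciding analysis: the between-arm difference over weeks 5 to 16, adjusted for the baseline mean, from the mixed model already planned, with home as a random effect.
- Test the other two outcomes in a fixed order, each only if the one before is significant, or label them secondary.
- Report weekly and before/after comparisons as descriptive estimates with confidence intervals.

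This takes about a paragraph and no new data. The price is that an isolated weekly, before/after or secondary result can no longer be claimed as proof of effect.

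Keeping three equal outcomes would cost more. Holding 5% by Bonferroni needs 0.05 / 3 = 0.0167 per test. At 80% power that multiplies the sample size by (2.394 + 0.842)² / (1.960 + 0.842)² ≈ 1.33, whatever the effect size.
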